## Abstract

**Background:**

The use of spinal cord stimulation (SCS) in patients with refractory angina pectoris (RAP) is still under debate. Studies up to date have shown a positive effect with an improvement in quality of life. However, no double blinded randomized controlled trials have been performed.

**Hypothesis & Methods:**

The objective of this trial is to investigate if high density SCS leads to a significant reduction in the amount of myocardial ischemia in patients with RAP. Eligible patients must meet the criteria for RAP, have proven ischemia and a positive transcutaneous electrical nerve stimulator treadmill test. Patients who meet the inclusion criteria will receive an implanted spinal cord stimulator. Patients receive 6 months of high density SCS and 6 months of no stimulation using a cross‐over design. The order of the treatment options is determined using randomization. The primary endpoint is the effect of SCS measured by the change in percentage of myocardial ischemia using myocardial perfusion positron emission tomography scan. Key secondary endpoints are patient related outcome measures, major cardiac adverse events and safety endpoints. The follow‐up period is 1 year for the primary and key secondary endpoints.

**Results:**

The SCRAP trial began enrollment on December 21, 2021 and is set to complete the primary assessments in June 2025. To date, January 2, 2023, 18 patients have been enrolled in the study and 3 patients have completed the 1‐year follow‐up.

**Conclusions:**

The SCRAP trial is an investigator‐initiated, single‐center, double‐blind, placebo‐controlled, and cross‐over randomized controlled trial investigating the efficacy of SCS in patients with RAP. (ClinicalTrials. gov Identifier: NCT04915157)

## INTRODUCTION

1

Coronary artery disease (CAD) is one of the most prevalent diseases worldwide. Due to advancements in treatment options mortality and morbidity rates in this patient population have steadily declined. However, up to 20% of patients with stable CAD have persisting angina symptoms.^1^ It is estimated that 5%–10% of patients with stable CAD who remain symptomatic despite optimal treatment have “refractory angina pectoris” (RAP).^2^, ^3^ RAP was defined in 2002 by Mannheimer et al as a chronic condition (>3 months) characterized by diffuse coronary artery disease in the presence of proven ischemia, which is not amenable to a combination of medical therapy, angioplasty or coronary bypass surgery.^2^ In absolute numbers up to 1.8 million people in the United States (US) have RAP with 50 000–100 000 new cases each year in the United States and 30 000–50 000 new cases each year in Europe.^4^ Patients with RAP have a severely limited quality of life due to the daily, persisting angina symptoms with its inherent physical limitations.

Spinal cord stimulation (SCS) is a last resort treatment option for this patient population in which no other treatment options are currently available. SCS is a device with a lead located in the higher thoracic epidural space and an implantable pulse generator (IPG) in the abdomen or buttock that provides stimulation at the level of the myocardial afferent sympathetic neurons (C7–Th1). The potential beneficial effects of SCS are based on four possible mechanisms: reduction of myocardial oxygen demand, reduction of pain perception, and a decrease in sympathetic tone and an improvement in the coronary microcirculatory blood flow.^5^, ^6^

The majority of research into the effect of SCS on RAP has been observational in nature. To date three placebo‐controlled randomized controlled trials have been performed and one study compared SCS with usual care.^6^, ^7^, ^8^, ^9^ In the three placebo‐controlled studies various settings of spinal cord stimulation (normal, subthreshold, and sham) have been compared with differing results.^7^, ^8^, ^9^ Reduction in the number and severity of angina symptoms was proven in all studies, but it is not clear if there is a placebo effect as suggested by the study of Zipes et al.^9^ In this study two modes of stimulation; high—conventional use of spinal cord stimulation, and low—spinal cord stimulation during 1 min each day, were compared with no significant differences between the two groups after 6 months of treatment.^9^ Whilst the two other studies comparing different levels of spinal cord stimulation did find significant differences between the groups.^7^, ^8^ These conflicting results make interpretation difficult, especially taking into account that the studies were underpowered and had slow patient inclusion rates which led to early termination of the studies. Despite the limitations of these individual studies two systematic reviews confirm that there is a significant improvement in exercise duration, Canadian Cardiovascular Society (CCS) class, Visual Analog Scale (VAS) score, daily angina episodes, angina frequency, daily nitrate consumption, disease perception and treatment satisfaction in RAP patients with SCS.^10^, ^11^

Although the exact working mechanism of SCS in RAP has not been elucidated studies have repeatedly shown an improvement in the quality of life and a reduction in angina symptoms.^7^, ^8^, ^9^, ^11^, ^12^, ^13^ It is unclear if SCS leads to reduction in the amount of myocardial ischemia. One study by Diedrichs et al. determined the effect of SCS based on the amount of myocardial ischemia using Methoxyisobutylisonitrile single photon emission computed tomography (MIBI‐SPECT).^14^ All patients were treated with SCS and MIBI‐SPECT was performed at baseline, 3 and 12 months. After 12 months, there was a significant reduction in the amount of myocardial ischemia that was not seen at 3 months. Because the reduction of myocardial ischemia was only seen at 12 months, the authors concluded that this effect might not have been a direct effect of SCS, but rather due to better coronary collateralization created by enhanced physical activity. Thus, the question remains whether SCS actually reduces the amount of myocardial ischemia.

The recently published European Society of Cardiology (ESC) guideline “Chronic Coronary Syndromes” describes varying levels of evidence with regard to treatment options in patients with RAP. The ESC guideline concludes that SCS may be considered (Class of recommendation IIB; level of evidence B).^15^ It summarizes that “Larger RCTs are required to define the role of each treatment modality for specific subgroups, to decrease nonresponder rates and ascertain benefit beyond potential placebo effects,” confirming the need for additional studies.^15^

The type of SCS traditionally used in patients with RAP is conventional stimulation. With this type of stimulation the patient will feel paresthesia at the target area. For this study a paresthesia free form of stimulation, high density (HD) stimulation, will be applied. Based on previous experience it is a viable treatment modality, it allows adequate blinding of patients because no paresthesia are felt and the patient can be fully informed about the fact that the spinal cord stimulator will be turned off for a period of 6 months.^16^ This is in contrast to previous studies in which blinding of patients has been problematic due to the paresthesia felt by the patient.^6^, ^7^, ^8^, ^9^

The aim of this investigator‐initiated, single‐center, placebo‐controlled, double‐blind, cross‐over, randomized controlled trial is to determine if high density spinal cord stimulation, a paresthesia free form of stimulation, leads to a significant reduction in the amount of myocardial ischemia in patients with RAP. The trial has been registered at ClinicalTrials.gov with NCT identifier NCT04915157.

## METHODS

2

### Study design

2.1

The primary objective of this study is to determine the effect of SCS in patients with RAP on the percentage of myocardial ischemia measured using a myocardial perfusion positron emission tomography (PET) scan. Patients with RAP referred to our hospital (Catharina hospital, Eindhoven, the Netherlands) will be screened for eligibility to participate in the study. The inclusion criteria must be met, meaning stable angina pectoris CCS class III or IV during at least the previous 3 months, a coronary angiogram (CAG) performed within the last 12 months with significant CAD not suitable for intervention, optimal antianginal medication and proven ischemia using MIBI‐SPECT, perfusion magnetic resonance imaging (MRI), myocardial perfusion PET scan or a fractional flow reserve (FFR) positive lesion (<0.80) with no intervention options. Tables 1 and 2 give a complete overview of the inclusion and exclusion criteria. To determine if patients meet the afore mentioned criteria the referral letter and CAG images will be evaluated by one of the interventional cardiologists (two in case of doubt).

**Table 1 clc24016-tbl-0001:** Inclusion criteria.

Refractory Angina Pectoris: ○ Stable angina pectoris CCS class III or IV, with a minimum of five episodes of angina pectoris over the course of 1 week, during a minimum period of 3 months before screening; ○ CAG performed within the last 12 months showing significant coronary artery disease defined as at least one coronary artery stenosis of >75% or 50%–75% with proven ischemia (see below), not suitable for revascularization. Confirmed by one (or two in case of doubt) interventional cardiologist based on CAG images; ○ Optimal antianginal medication. Patients should at least use the maximal tolerable dose of a beta‐blocker, calcium channel blocker and short‐ and/or long‐acting nitrate. If the patient does not use one of these groups of medication the reason (side‐effects) should be clear.
Proven ischemia: ○ MIBI‐SPECT: SSS of at least 1, in combination with SDS of at least 1 (1–4 mildischemia, >4 moderate to severe ischemia). ○ Fractional flow reserve: <0.80, with no intervention options (determined by interventional cardiologist). ○ MRI perfusion: ≥1 segment of subendocardial hypoperfusion during stress perfusion, not present at rest and no matching fibrosis (using 16 segment AHA heart model). ○ Myocardial perfusion PET: Semi‐quantitative measurement: SSS of at least 1, in combination with SDS of at least 1 (1–4 mild ischemia, >4 moderate to severe ischemia). Quantitative measurement: reduced myocardial perfusion reserve.
No revascularization (PCI and/or CABG) performed between ischemia testing and study inclusion.
Age >18 years.

Abbreviations: CABG, coronary artery bypass grafting; CAG, coronary angiogram; MIBI‐SPECT, methoxyisobutylisonitrile single photon emission computed tomography; MRI, magnetic resonance imaging; PCI, percutaneous coronary intervention; PET, positron emission tomography; SDS, summed difference score; SSS, summed stress score.

**Table 2 clc24016-tbl-0002:** Exclusion criteria.

Acute coronary syndrome during the 3‐month period before screening.
Life expectancy less than 12 months.
Inability to perform a 6‐min walking test.
Inability to give informed consent.
No proven ischemia (see Table 1 Inclusion criteria).
Spinal cord disease which could prevent correct positioning of the lead in the epidural space; to be determined by the anesthesiologist performing the implantation.
Anticoagulation therapy that cannot be stopped/bridged before spinal cord stimulator implantation.
Inadequate paresthesia coverage, during implantation, of the thoracic region where angina complaints are localized.
Pregnancy.
Mild Cognitive Impairment or dementia.
Concomitant symptomatic valvular heart disease including severe aortic stenosis and/or regurgitation, severe mitral valve stenosis and/or regurgitation or severe tricuspid valve regurgitation.

#### Standardized TENS treadmill test

2.1.1

Eligible patients will be invited to the outpatient clinic to perform a standardized transcutaneous electrical nerve stimulation (TENS) treadmill test. The standardized TENS treadmill test is used as a screening tool, as advised by Mannheimer et al in the ESC report, to determine if the patient is eligible for an implanted spinal cord stimulator.^2^ The standardized TENS treadmill test is used to induce angina pectoris and determine what the effect is of TENS on the time to resolution of angina pectoris. For the standardized TENS treadmill test two adhesive electrodes are applied to the chest and connected to a battery‐operated TENS (eco 2, Schwa‐medico Netherlands BV). The TENS settings are programmed with a pulse width of 200µs and a frequency of 2 Hz. The patient is asked to start walking on a treadmill (Enraf‐Nonius BV) with an initial speed of 3.5 km/h. The speed is increased every 30 s with 0.5 km/h to a maximum of 5.5 km/h. If angina pectoris has not been induced the inclination angle is increased with 1% every 30 s. Once angina pectoris is induced the treadmill will be stopped, followed by switching on the TENS with an amplitude of 40 mA. A timer is started and the patient will be asked to comment when the angina pectoris is no longer present.

Before the standardized TENS treadmill test the patient will fill out the TENS questionnaire (Appendix 1). The answer to question 2 of the TENS questionnaire—usual time until symptom resolution without use of short‐acting nitrates, will be compared to the time it takes for the symptoms to disappear after initiation of TENS. There are three possible test outcomes:
(a)Positive: equal to or more than 50% reduction in the time from onset of angina pectoris until resolution of angina pectoris after TENS initiation, compared to the “normal” time it takes for angina pectoris to resolve.(b)Dubious: less than 50% reduction in the time from onset of angina pectoris until resolution of angina pectoris after TENS initiation, compared to the ‘normal’ time it takes for angina pectoris to resolve.(c)Negative: no reduction or increase in the time from onset of angina pectoris until resolution of angina pectoris after TENS initiation, compared to the “normal” time it takes for angina pectoris to resolve.

Patients with a positive standardized TENS treadmill test are eligible for participation in the study and a myocardial perfusion PET scan is performed to determine the amount of myocardial ischemia present. Patients with a negative standardized TENS treadmill test are excluded from the study. Patients with a dubious standardized TENS treadmill test will receive TENS treatment in an ambulatory setting for a duration of 2 weeks. After this period the effect of TENS will be re‐evaluated by the same team to determine whether the effect was positive or negative (a dubious test result is not possible). If the effect is positive the patient is eligible and a myocardial perfusion PET scan will be performed 1 month after termination of TENS treatment (washout period to prevent possible lingering effects of the TENS treatment) (Figure 1).

**Figure 1 clc24016-fig-0001:**
[figure not shown]
Flowchart of the screening process for inclusion into the SCRAP trial; patients eligible for participation in the SCRAP trial. A standardized TENS treadmill test is performed. Patients with a dubious standardized TENS treadmill test will be included if they have a positive result after 2 weeks of ambulatory TENS. Patients with a positive standardized TENS treadmill test will undergo a cardiac PET. CCS, canadian cardiovascular society; FFR, fractional flow reserve; MIBI‐SPECT, methoxyisobutylisonitrile single photon emission computed tomography; MRI,  magnetic resonance imaging; NRS, numeric rating scale; PET, positron emission tomography; RAND‐36, RAND 36‐item Health Survey; SAQ, seattle angina questionnaire; TENS, transcutaneous electrical nerve stimulation.

If myocardial ischemia is proven, with myocardial perfusion PET scanning, the patient is included. All participating patients will receive an implanted spinal cord stimulator. The total duration of the study is 12 months during which patients will receive 6 months of HD SCS, a paresthesia free form of SCS, and 6 months of no stimulation using a cross‐over design. To determine the order of the treatment options randomization using the online program Research Manager will be performed (Figure 2). The randomization is done by the study nurse. The study nurse will be the only person of research team that knows to which arm the patient has been randomized. This same study nurse is also responsible for inputting the correct programming of the SCS based on the randomization. The patient and the remaining members of the research team are blinded to the randomization process. During the study period of one year the patient will have use of the patient programmer. To ensure blinding of the patient remains intact, during the “SCS OFF” or placebo period, a non‐existent second lead will be programmed as being active, whilst leading to no actual SCS. This enables the use of the patient programmer during the “SCS OFF” or placebo period and also keeps the blinding of the patient intact.

**Figure 2 clc24016-fig-0002:**
[figure not shown]
Flowchart of randomization process and study design; after informed consent is given a SCS is implanted. Patients are randomized into arm A or B with 6 months of spinal cord stimulation and 6 months of no stimulation or vice versa. At 6 and 12 months measurements (including PET, 6‐MWT, SAQ, NRS, CCS, and RAND‐36) are performed. The study period is 12 months. 6‐MWT, 6 min walking test; NRS, numeric rat; PET, positron emission tomography, RAND‐36, RAND 36‐item Health Survey; SCS, spinal cord stimulator.

#### Spinal cord stimulator implantation

2.1.2

The spinal cord stimulator system consists of an implantable pulse generator (IPG) (PrimeADVANCED™ SureScan® MRI Medtronic), a single lead (Vectris Compact™ SureScan MRI Medtronic) and a patient programmer (myStim Patient Programmer & ADVANCED™ Antenna Medtronic). The spinal cord stimulator implantation will take place in an operating room in accordance with national guidelines concerning aseptic preparations. During the procedure the patient is asked to lie in a prone position to increase the thoracic kyphosis. Moderate sedation is applied using a combination of propofol and remifentanil, secondary field blocks and wound infiltration with local anesthetics will be used to provide analgesia. Sedation levels and vital signs are controlled and monitored by an experienced nurse. A Tuohy needle is used to enter the epidural space at the level of thoracic vertebrae (Th) 7–8. Entrance into the epidural space is gained using loss of resistance and confirmed by advancing a guide wire through the Tuohy needle under fluoroscopic guidance. Next the guide wire is removed and the lead is advanced into the epidural space with the cephalad tip positioned paramedian to the left side at the level of C7‐Th1 using fluoroscopic guidance. To determine if the position of the lead is correct sedation is temporarily lifted and using an external programmer (Intellis Wireless External NeuroStimulator (WENS), Samsung Programsystem and Communicator) stimulations are given. The aim is to achieve a paresthesia coverage of the target area (left side of the chest) of at least 80% and subtle modifications of the lead position are performed to reach the optimal coverage based on feedback from the patient during test stimulation. When the optimal position of the lead has been determined the lead is fixated at the thoracodorsal fascia, subcutaneously tunneled and connected to the IPG pocket. The usual subcutaneous position of the IPG is the left buttock. After the implantation has been completed the patient is monitored on the ward and an X‐ray is made to confirm the position of the lead. Depending on the randomization the correct settings will be input by the unblinded study nurse (Appendix 2 gives a detailed description of the spinal cord stimulator settings). In general, the patient will be discharged from the hospital on the same day with instructions on the use of the patient programmer and what to do if complications and/or questions arise.

### Endpoints

2.2

#### Primary endpoint objective

2.2.1

The primary objective of this study is the effect of SCS in patients with RAP measured by the change in the percentage of myocardial ischemia (% of the left ventricular myocardium) using myocardial perfusion PET scan at the end of the six‐month period of treatment with SCS compared with baseline.

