### Sample size calculation

2.4

Currently, no data with regard to the percentage of myocardial ischemia (as % of the left ventricular myocardium) present in patients with RAP using myocardial perfusion PET scan as imaging modality are available. The data available on this subject is with the imaging modality MIBI‐SPECT. The percentage of myocardial ischemia (as % of the left ventricular myocardium) present in patients with refractory angina pectoris using MIBI‐SPECT ranges from 6.12% (standard deviation of 3.7)^18^ up to 14.01%.^19^ Combining this data, it translates into an average percentage of myocardial ischemia of 10% with a standard deviation of 7.

Using these clinical assumptions (average percentage of myocardial ischemia of 10% and a standard deviation of 7) and the typical assumptions (paired, two‐tailed *T* test, *α* .05 and power .80) a sample size of 32 patients per arm (total 64 patients) could detect a relative reduction in percentage of myocardial ischemia of 25%. Assuming a 10% patient drop‐out in the analysis, this means a total of 72 patients should be included in the study.

Due to the study design using cross‐over, it is theoretically possible that a carry‐over and/or period effect could occur. We will apply the two‐stage approach as proposed by Grizzle et al to assess the carry‐over and period effect.^20^ To assess the carry‐over effect we will first determine the summed effect over the two periods and compare these between the two groups (A and B). In the same way we will assess the period effect by determining the summed effect over the two groups and compare these between the periods. When analyses show that the carry‐over effect as well as the period effect are negligible, we will use a paired, two‐tailed Students’ *T* test for the main outcome parameter. If a significant carry‐over effect is found, only data from the first period will be analyzed. Due to the long study period of 6 months before performing the PET scan after cross‐over has taken place, the assumption is that there will not be a carry‐over effect.

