## LIMITATIONS

5

There are a number of limitations with regard to the SCRAP trial. One limitation is the difference in myocardial ischemia on which the sample size calculation is based. The power of the study is based on a relative reduction in myocardial ischemia of 25% after treatment with SCS, in absolute numbers a reduction from 10% to 7.5% of myocardial ischemia. Whilst this is a relatively modest difference, it is deemed clinically relevant. Patients with more than 10% myocardial ischemia have a worse prognosis in comparison to patients with less than 10% myocardial ischemia,^15^ making the chosen difference clinically relevant. A second limitation of the study is the single‐center design and the reason for this choice is twofold. Firstly the number of patients meeting the selection criteria is expected to be low. Second, the implantation of spinal cord stimulators should be limited to specialized centers to reduce the risk of device‐related complications and the chosen center for the SCRAP trial is such a specialized center.^26^, ^27^

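### The primary endpoint is written as a change from pre-implant baseline, which conflicts with the placebo-controlled cross-over design and analysis; the ON versus OFF contrast is never named

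*Protocol article*

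**What the plan says.** - **Endpoint (section 2.2.1).** The outcome is the change in the percentage of left ventricular myocardium that is ischaemic on PET, at the end of the six-month "period of treatment with SCS compared with baseline". The OFF period is not mentioned.
- **Baseline scan (section 2.1.1, text after Figure 1).** The baseline PET decides entry: "If myocardial ischemia is proven, with myocardial perfusion PET scanning, the patient is included". Implantation follows it.
- **Design (same text).** Over 12 months "patients will receive 6 months of HD SCS, a paresthesia free form of SCS, and 6 months of no stimulation", in randomised order. OFF is called the placebo period. The abstract, introduction and conclusion all call the trial placebo-controlled.
- **Scans (Figure 2 legend; section 2.3).** "At 6 and 12 months measurements (including PET, 6‐MWT, SAQ, NRS, CCS, and RAND‐36) are performed". Every completer therefore has one end-of-ON scan and one end-of-OFF scan.
- **Analysis (section 2.4).** A two-stage cross-over approach is planned. For carry-over, "we will first determine the summed effect over the two periods and compare these between the two groups (A and B"). If carry-over and period effects are negligible, a paired two-tailed t test is applied to the main outcome, without saying which two measurements form the pair. If carry-over is significant, only first-period data are used.
- **Powered effect (section 5).** The power is "based on a relative reduction in myocardial ischemia of 25% after treatment with SCS, in absolute numbers a reduction from 10% to 7.5"%.

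**The concern.** The endpoint sentence is the only place where the primary contrast is stated, and it describes a before-after change on active treatment. Such a change includes whatever would have happened without stimulation:

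- **Regression to the mean**, because patients enter only if the baseline scan shows ischaemia.
- **Response to the implant or to being treated**, because baseline precedes surgery.
- **Time trend**, and unequally so: the end-of-SCS scan falls at 6 months in one sequence and at 12 months in the other.

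The introduction shows why this matters. It describes an earlier SPECT study in which every patient was stimulated and ischaemia had fallen from baseline at 12 months but not at 3. That study's authors doubted that the fall was a direct effect of stimulation, and the protocol treats the question as still open. A primary test against baseline would leave it open again. There is a second risk: with two incompatible descriptions in the protocol, the contrast could be settled after the data are seen.

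**Working it through.** **1. The two sections side by side.** The carry-over test compares period sums between sequence groups, and the period test compares periods. Both belong to an analysis of ON against OFF and need the OFF scans. The first-period fallback shows the conflict most clearly. Patients randomised to OFF first have no end-of-SCS scan in period 1, so the endpoint of section 2.2.1 is undefined for about half the trial. Under an ON versus OFF contrast the fallback is at least defined, as a comparison of the two groups at 6 months.

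**2. The plan's own sample size.** Inputs from section 2.4: mean 10%, SD 7, relative reduction 25%, two-sided alpha 0.05, power 0.80, dropout 10%.
- Difference: 0.25 × 10 = 2.5 points.
- Paired t test with SD of the difference 7: noncentrality = 2.5 × √64 / 7 = 2.857, giving power 80.3% at 64 pairs (79.7% at 63). The stated 64 reproduces.
- Dropout: 64 / 0.9 = 71.1, rounded up to 72. This also reproduces.
- The formula is the same for ON minus baseline and ON minus OFF, so 64 does not reveal which contrast was meant.
- SD 7 is derived from SPECT values of ischaemia in patients and is not stated to be an SD of differences. If it is the between-patient SD, the SD of the difference is 7√(2(1−ρ)). The required pairs are then 126, 95, 64 or 33 for assumed ρ of 0, 0.25, 0.5 or 0.75.

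**3. Regression to the mean (illustration; inputs assumed, not in the document).** Take a normal distribution before selection with mean 9 and SD 7, an entry cut at 1.5% of the left ventricle, and test-retest correlation ρ of 0.8 or 0.5.
- Expected fall = (1−ρ) × σ × φ(a)/(1−Φ(a)), with a = (1.5 − 9)/7 = −1.071.
- φ(a)/(1−Φ(a)) = 0.2247/0.8580 = 0.262, and 7 × 0.262 = 1.83.
- ρ = 0.8: 0.2 × 1.83 = 0.37 points. ρ = 0.5: 0.5 × 1.83 = 0.92 points.

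**4. Chance of p<0.05 against baseline when ON and OFF do not differ (64 pairs).** Noncentrality = shift × 8 / SD.

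| Shift (points) | SD of change | Noncentrality | P(p<0.05) |
|---|---|---|---|
| 0.37 | 7 | 0.42 | 7.0% |
| 0.37 | 4.35 (implied by ρ = 0.8 after selection) | 0.67 | 10.2% |
| 0.92 | 7 | 1.05 | 17.8% |
| 0.92 | 6.69 (implied by ρ = 0.5 after selection) | 1.10 | 19.1% |
| 1.5 (assumed total non-specific fall) | 7 | 1.71 | 39.3% |

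The SDs implied by ρ are √[(1−ρ)² × 5.65² + (1−ρ²) × 7²], where 5.65 is the SD of the selected baseline values. An ON versus OFF test would stay at 5% in every row, absent period and carry-over effects.

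**5. Power for ON versus OFF if OFF shares part of the 2.5-point fall (64 pairs, SD 7).**
- None shared: difference 2.5, power 80.3%.
- 25% shared: 2.5 × 0.75 = 1.875, power 56.0%.
- 50% shared: 2.5 × 0.5 = 1.25, power 29.0%.

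**The case against.** The best defence is that section 2.2.1 names the outcome variable and section 2.4 sets the comparison. Change from baseline is compatible with a placebo comparison, since (ON − baseline) − (OFF − baseline) = ON − OFF. On that view one clause is missing and ON versus OFF was intended all along. Much of this stands: the cross-over analysis makes ON versus OFF the likely intention. But no section writes that comparison out, and the t test leaves its pair unnamed, so section 2.4 does not correct section 2.2.1.

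A reader might infer more than the document supports:

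- **That the OFF scans will go unused and randomisation plays no part.** The two-stage analysis needs both. What can be shown is a conflict between two sections.
- **That the fall from 10% to 7.5% proves a before-after intention.** It fits ON versus OFF equally well, with 10% as the unstimulated level.
- **That later optimisation of medication would count as an SCS effect.** Maximal tolerable antianginal medication is an entry criterion in Table 1, and no later optimisation is described.
- **That false-positive rates of 39% or more are expected.** They rest on hypothetical shifts. The only bias estimated here, regression to the mean, gives roughly 7-19%, itself under undocumented inputs.
- **That the secondary outcomes have the same fault.** Table 3 states no contrast for them, which an article may leave to the full protocol.

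**Conclusion.** The point holds as a conflict that must be resolved. The endpoint definition, taken as written, is an uncontrolled before-after test in a trial presented as placebo-controlled, and it cannot be reconciled with the cross-over analysis or its first-period fallback. The document does not establish that the investigators will analyse it that way.

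The size depends on assumptions. Regression to the mean of 0.4 to 0.9 points (assumed pre-selection distribution, entry cut and correlation) would raise the false-positive rate from 5% to roughly 7-19%. Implant response and time trend would add to that by an unknown amount; an assumed total of 1.5 points gives 39% at SD 7. The stated 64 (72 with dropout) carries over to ON versus OFF only if 7 is the SD of that difference and the full 2.5 points is the ON-OFF effect.

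**What to change.** - **Section 2.2.1:** define the primary contrast as the within-patient difference in percentage ischaemic left ventricular myocardium, end of SCS-ON minus end of SCS-OFF, from the 6- and 12-month PET scans. Report change from baseline as supportive.
- **Section 2.4:** name that pair in the t test.
- **Sections 2.4 and 5:** state that 2.5 points and SD 7 refer to the ON-OFF difference. If either does not, restate the power accordingly, using the calculations above as a guide.

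**Cost:** an amendment of wording, with no new scans or visits. It should not be promised that the sample size is unaffected, because relabelling the 2.5 points as ON minus OFF is a substantive assumption. When the article was written, 18 patients were enrolled and 3 had completed one year, so an early change was feasible. It should in any case be made before the investigators are unblinded.
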